### Randomisation and blinding

Computer-generated random sequence randomisation (central) will be performed, after giving informed consent. Due to the expected large sample size, we will use simple randomisation. The allocation ratio will be 1:1. No stratification or blocking will be applied.

In the study, participants will be blinded to the knowledge of the details of differences between the interventions. Everyone else (outcome assessors, caregivers, and data analysts) will be blinded regarding the allocation.

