### Sample size calculation, interim, and final analyses

The primary outcome is estimated to occur in 20% of COVID-19-infected cases (≥ 60 years of age) receiving the standard of care based on Chinese reports [5]. Due to the lack of data, we hypothesised that our intervention would result in a 50% risk reduction. Considering one interim analysis on efficacy (with the Pocock correction), 90% power, 5% alpha (superiority design, two-sided), a dropout rate of 20% [28, 29], and assuming 10% incidence of COVID-19 in the target population, the estimated sample size is 3788 (rounded up to 3800) subject per study arm. The calculation was performed by Stata (version 15, Philadelphia, the USA).

We plan to hold three interim analyses: the first for sample size re-estimation at 5% of the target sample size due to the dropout rate, the second for safety assessment at 10% of the target sample size, and the third for efficacy assessment and sample size reestimation at 50% of the target sample size. Early stopping will be executed if (1) safety concerns arise during the interim analysis; (2) the statistical power reaches at least 90% and *p* < 0.05 at the efficacy interim analysis (stopping for benefit); (3) the statistical power does not reach 10%, *p* > 0.05, and the event number does not reach the assumed 10% for the whole population at the efficacy interim analysis (that is, 380 events for the primary outcome; otherwise, the interim analysis is postponed and repeated when the event number reaches 380 events) (stopping for futility); and (4) the consequences of the pandemic make further recruitment or follow-up impossible (stopping for unfeasibility).

In the final analysis, the intention-to-treat analysis will be favoured over per-protocol (or “as-treated”) analysis. We expect a full dataset for the primary endpoint (since the Hungarian Ministry of Interior will provide these data). If for any reason, data will be missing for the primary outcome, we will use available case analysis. The “last observation carried forward” strategy will be followed to impute missing data for other outcomes measured during the study. Missing more than one consecutive interventions after the initial assessment or withdrawal of consent during follow-up results in the dropout of the patients unless hospitalisation is required in the meantime.

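### The futility criterion is inverted and conflicts with itself: too few events is required for stopping, yet the same sentence postpones the look until that number is reached

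*Protocol article*

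**What the plan says.** The rule stands in the protocol article, Methods, under Sample size calculation, interim, and final analyses. Three interim analyses are planned; the third, at 50% of the target sample size, is for efficacy and sample size re-estimation. The futility criterion applies only at that look. It joins three conditions with 'and': "the statistical power does not reach 10%, *p* > 0.05, and the event number does not reach the assumed 10% for the whole population". The bracket that follows equates the threshold with 380 events for the primary outcome and continues: "otherwise, the interim analysis is postponed and repeated when the event number reaches 380 events".

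The design inputs are in the same section. On the control rate: "The primary outcome is estimated to occur in 20% of COVID-19-infected cases". On the effect: "we hypothesised that our intervention would result in a 50% risk reduction". On infections: "assuming 10% incidence of COVID-19 in the target population". Dropout is put at 20%, power at 90% and two-sided alpha at 5% with a Pocock correction for one efficacy interim, giving 3788 subjects per arm, rounded up to 3800. The section on Randomisation and blinding adds: "The allocation ratio will be 1:1". A separate fourth criterion covers stopping because the pandemic makes recruitment or follow-up impossible. No other section restates or corrects the futility rule.

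**The concern.** A stopping rule should give one action for each state of the data. Here a low event count combined with a flat result is the state in which the main clause stops the trial. A low event count is also the only state in which the bracket's instruction to wait for 380 can be carried out. Two people applying the sentence to identical data could stop the trial or continue it, and the choice would then be made with the results in view.

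The direction is also the reverse of what a futility rule needs. A shortage of events is normally a reason to withhold a futility judgement; here it is required for one. Reaching the threshold removes the possibility of a futility stop, so the postponed look cannot do what it was postponed for. What is at stake is wrongly abandoning an effective intervention if the look falls when few cases have accrued.

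**Working it through.** **1. The plan's sample size reproduces.** The Pocock nominal level for two looks is 0.0294 two-sided (a standard constant, not printed in the article), so z = 2.178; for 90% power z = 1.282. With 20% versus 10%, mean 15%:

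n = [2.178 × √(2 × 0.15 × 0.85) + 1.282 × √(0.20 × 0.80 + 0.10 × 0.90)]² / 0.10² = 303 infected per arm (302.99 with unrounded z values).

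303 / 0.10 / (1 − 0.20) = 3787.5, rounded up to 3788. This matches the stated figure, so the inputs are read as the authors meant them.

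**2. The rule as a truth table**, given power below 10% and p > 0.05:

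| Primary events | Stop condition met? | Waiting for 380 meaningful? |
|---|---|---|
| 57 | yes | yes |
| 114 | yes | yes |
| 379 | yes | yes |
| 380 | no | no, already reached |
| 450 | no | no, already reached |

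Below 380 both actions apply. From 380 upwards a futility stop is impossible.

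**3. Which rows are expected?** Average event risk among the infected is 15% under the planned effect (mean of 20% and 10%) and 20% if there is no effect.

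- Half-way look: 3800 × 0.10 = 380 infections; primary events 380 × 0.15 = 57 to 380 × 0.20 = 76. After 20% dropout: 304 infections, 46 to 61 events.
- Full enrolment: 7600 × 0.10 = 760 infections; 114 to 152 events. After dropout: 91 to 122.

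The count is expected to be below 380 at every stage. The number 380 is the expected number of infections at the half-way look, but the article labels it as primary-outcome events. Reaching 380 primary events at 10% incidence would need 380 / (0.10 × 0.20) = 19,000 to 380 / (0.10 × 0.15) = 25,333 subjects, before dropout.

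**4. Cost of a futility stop at low information.** The article does not define the power in this rule. Assumption: it is observed power at two-sided 0.05. Solving Φ(z − 1.96) + Φ(−z − 1.96) = 0.10 gives |z| = 0.652, which also implies p > 0.05. The design drift is 2.178 + 1.282 = 3.46, so at information fraction t the interim z has mean 3.46√t. The wrong-stop chance under the planned effect is Φ(0.652 − 3.46√t) − Φ(−0.652 − 3.46√t). Overall power is from simulation with the Pocock bound 2.178 at both looks. If 3800 subjects are otherwise as planned, t = 0.50 × incidence / 10%.

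| Information at the efficacy look | Incidence that would produce it | Wrong-stop chance | Overall power |
|---|---|---|---|
| 50% | 10% (as planned) | 3.5% | about 90% |
| 25% | 5% | 13% | about 81% |
| 17% | 3.4% | 20% | about 75% |
| 10% | 2% | 29% | about 66% |
| 5% | 1% | 38% | about 57% |

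Without the futility stop, power is 90% to 91% in every row. The 5% and 10% rows are information fractions at the efficacy look. They are not the planned interims at 5% and 10% of sample size, which concern dropout and safety.

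Reading the power condition instead as one-sided conditional power under the current trend gives wrong-stop chances of about 29%, 22%, 16%, 12% and 6% at 5%, 10%, 17%, 25% and 50% information.

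**The case against.** **The word 'otherwise' can be read charitably.** It may refer to failure of the whole conjunction: few events with a flat result means stop; few events without a flat result means postpone. That removes the head-on clash below 380. The text does not spell it out, however, and under this reading a futility stop is still barred once 380 is reached, where the instruction to wait is empty.

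**A reader might infer that the trial can stop for futility only when information is short, and never with adequate information.** The printed threshold does not support that. The design rests on about 606 × 0.15 = 91 primary events (303 infected per arm), so 379 events is about four times the design's full information. With 380 primary events as printed, a flat result at a well-informed look still meets the stop condition. The inference would hold only if 380 were re-read as infections.

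**A reader might also infer that the planned 90% power is lost.** At the planned 50% information it is not: power is 91.0% without the stop and 89.7% with it. The larger losses need low incidence or little follow-up at the look. That is plausible, since the Strengths and limitations section says the infection rate may deviate from 10%, but it is a departure from plan.

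**The calculation treats the rule as mechanical.** The Steering Committee decides on premature termination, and the same look includes sample size re-estimation, which the simulation omits. Both points stand as limits on the power figures. Against the first, the article says early stopping will be executed when a criterion is met.

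**Conclusion.** The criterion is wrong as written. A count below the threshold is both required for a futility stop and the only sensible ground for postponing the look, and a look repeated at 380 events cannot stop for futility. This follows from the sentence alone and needs no modelling. On the plan's own inputs the conflicting state is the expected one at every look.

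The numerical harm is conditional. It is about a 3.5% wrong-stop chance with power near 90% at the planned 50% information, rising to 13% to 38% with power about 81% down to 57% if the look carries only 25% down to 5%. These figures assume observed power as the meaning of the undefined power condition, the planned 20% versus 10% effect, and mechanical application of the rule. The defect should be corrected, but it does not show that the trial is underpowered as planned.

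**What to change.** Reverse the count condition and separate the two actions, for example: if the required count has not been reached at the planned efficacy look, the look is postponed and no futility decision is made; if it has been reached, and power is below 10% and p > 0.05, the trial stops for futility. Low incidence or failed recruitment would be handled under the fourth criterion, unfeasibility.

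Reconcile the required count in the same edit, stating whether it counts infections or primary-outcome events. If 380 primary events were kept, the corrected futility look would not be expected within the planned 7600 subjects. State also what is meant by power in this rule.

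The cost is a rewrite of one criterion. The downside is that no futility stop is possible before the required count is reached.

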### Strengths and limitations

We aim to apply lifestyle interventions considered to be safe in a broad population of subjects exposed at high risk of a severe course of COVID-19. The expected health benefits of the interventions considerably exceed its potential harms. With this study design, we can evaluate the effectiveness of (1) the offer of lifestyle intervention vs (2) that of the actual uptake of or compliance to the lifestyle intervention. We expect that the moderate intensity of the personalised multicomponent lifestyle intervention will maximise the effectiveness and, at the same time, prevents low adherence. In addition to the expected beneficial effects regarding the infection, other protective changes are likely regarding cardiovascular and malignant morbidity and mortality on the long-term. The interventions are easy to be delivered while being affordable and implementable for the vast majority of the population.

We expect that there will be limitations in this study [30]. We define cross-contamination that participants on different arms deliberately and unknowingly communicate with each other, leading to the loss of the true effect of lifestyle interventions. To minimise the risk of cross-contamination, we decided to include only one subject from communities with multiple potential candidate participants. Although we can evaluate the actual uptake of the lifestyle interventions, its validity is uncertain due to the patient-reported nature of the data. We cannot anticipate the climax of the epidemics so that the infection rate of the target population may deviate from the assumed 10%. To overcome this, we use sample size-readjustment adaptive design, which may settle the problem with the unpredictable dropout rate as well (although this method cannot counteract chronological changes in the dropout rate throughout the evolution of the pandemic). All data on secondary outcomes are provided by participants and other, less reliable indirect data sources. We anticipate that volunteers give a representative sample of the target population, but we cannot exclude that our study population will be somewhat better educated and highly motivated. Despite the thorough training of the operators, inter-operator variability may be present.

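### The futility and postponement rule sets its threshold at 380 primary-outcome events, but 380 is the expected number of COVID-19 infections at the half-way look; that many primary events cannot be reached in the planned sample

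*Protocol article*

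**What the plan says.** All the design inputs are in the section on sample size calculation, interim and final analyses. The event rate is conditional on infection: "The primary outcome is estimated to occur in 20% of COVID-19-infected cases" under standard care. On the effect, "we hypothesised that our intervention would result in a 50% risk reduction". Infection enters separately: "assuming 10% incidence of COVID-19 in the target population, the estimated sample size is 3788" per arm, rounded up to 3,800, with 20% dropout, 90% power, two-sided 5% alpha and a Pocock correction for one efficacy interim.

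The third interim analysis, for efficacy and sample size re-estimation, is placed at half the target sample. The futility item needs three things together: statistical power below 10%, p above 0.05, and an event number short of the assumed 10%. It spells the last one out as "380 events for the primary outcome; otherwise, the interim analysis is postponed and repeated when the event number reaches 380 events".

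The Outcomes section counts the primary endpoint only in laboratory-verified COVID-19 cases. Strengths and limitations adds that "the infection rate of the target population may deviate from the assumed 10%. To overcome this, we use sample size-readjustment adaptive design".

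**The concern.** The rule takes a percentage that describes infections and attaches it to primary-outcome events, which by the plan's own definition are a minority of infections. The resulting threshold is several times what the trial expects to observe.

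Two things are at stake. As a futility condition, a threshold that cannot be met is no condition: it is satisfied whatever the data show. As a trigger for a postponed or repeated look, it schedules an analysis that would not take place in the planned sample.

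The wording is also at odds with itself. A low count is listed among the grounds for stopping, yet the clause introduced by the word otherwise describes waiting for the count to rise to 380, which is what one would do when the count is low. A monitoring body with a low count could not tell which was meant.

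**Working it through.** **Inputs (sample size section unless stated).** Control risk among infected 20%; intervention risk 20% × (1 − 0.50) = 10%; average with 1:1 allocation 15%; incidence 10%; dropout 20%; 3,800 per arm, 7,600 in total; half-way look at 3,800 participants. One input is not in the document: the standard two-look Pocock nominal two-sided level, 0.0294.

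**1. Reproduce the plan's sample size.** For two proportions without continuity correction,

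n = [z(1−α/2) √(2 p̄(1−p̄)) + z(1−β) √(p₁(1−p₁) + p₂(1−p₂))]² / (p₁ − p₂)²

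With p₁ = 0.20, p₂ = 0.10, p̄ = 0.15, z = 2.178 (α = 0.0294) and 1.2816 (90% power):

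n = [2.178 × 0.5050 + 1.2816 × 0.5]² / 0.01 = 302.99, so 303 infected per arm.

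303 / 0.10 / 0.80 = 3,787.5, so 3,788. This is the stated figure. It confirms that 10% operates as the infection rate and that 20% and 10% are risks among the infected.

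**2. Where 380 comes from.** 3,800 × 0.10 = 380, the infections expected among 3,800 participants at the half-way look. (The same product gives infections per arm at full size.) The intervention-arm risk also happens to be 10%, but it applies to infected participants only, so it cannot be multiplied by 3,800.

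**3. Expected primary events = participants × 0.10 × risk among infected.**

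| | Infections | Design effect (15% average) | No effect (20% in both arms) |
|---|---|---|---|
| Half-way, 3,800 | 380 | 57 | 76 |
| Whole trial, 7,600 | 760 | 114 | 152 |

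If dropouts contribute no events, multiply by 0.80: about 46 and 91 under the design effect, about 61 and 122 with no effect.

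**4. Distance from the threshold.** Under the design effect, 380/57 = 6.7 times the half-way expectation and 380/114 = 3.3 times the whole-trial expectation. With no effect, 380/76 = 5 and 380/152 = 2.5.

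**5. What 380 primary events would require.**
- Participants: 380 / (0.10 × 0.15) = 25,333 under the design effect; 380 / (0.10 × 0.20) = 19,000 with no effect.
- Or incidence across all 7,600: 380 / (7,600 × 0.15) = 33%; 380 / (7,600 × 0.20) = 25%.
- Binomial probability of at least 380 events among 7,600 participants, in the most favourable case (no effect, no dropout, 2% per participant): below 10⁻⁵⁰.

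**6. What the rule then does.** The condition that the count falls short of 380 is practically always true, so the futility item reduces to power below 10% and p above 0.05. Any look made to wait for 380 events does not happen within 7,600 participants.

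**The case against.** Three points on the other side have force.

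*The interim analysis may still be held.* A reader might infer that the only efficacy interim, and the re-estimation tied to it, can never occur. The text does not go that far. The look is set at 50% of the target sample; the 380 clause sits inside the futility item; the item on stopping for benefit carries no event threshold; and an analysis that is repeated may already have been held once. On that reading only the later look is unreachable. This stands.

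*Low incidence alone does not stop the trial.* A reader might also infer that a shortfall in infections would by itself trigger futility. It would not, because the power and p-value conditions must hold too. As an illustration, take statistical power to mean observed power at two-sided 5%, which the document does not define. With a true 20% versus 10% effect and 1,900 per arm, simulation puts the chance of meeting both other conditions at about 2% with 10% incidence, 9% with 5% and 25% with 2%. The risk becomes material only well below the planned incidence. This stands as well.

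*114 is not a ceiling.* It assumes that the 50% reduction is real. With no effect, the case a futility rule exists for, the total is about 152. The dropout-reduced figures are also uncertain, because the plan expects complete primary-endpoint data from a ministry source, so dropouts may still contribute events.

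None of this rescues the threshold: 152 is still far below 380. Uncertainty about incidence does not help either, since 380 primary events need 2.5 to 3.3 times the assumed rate. Nor does the Strengths and limitations text strictly contradict the rule, because re-estimation at 50% appears in both sections; it does need to fit whatever a low count is meant to trigger.

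**Conclusion.** Wrong as written. The threshold is a count of infections labelled as a count of primary events, overstating the half-way expectation about 6.7-fold under the design effect and 5-fold with no effect. At the planned 7,600 participants it cannot be reached under either assumption. The event condition therefore does no work in the futility rule, a look deferred or repeated to 380 events would not occur in the planned sample, and the consequence of a low count is ambiguous.

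This rests on the plan's own 10% incidence, 20% control risk and 50% reduction; the exact match to 3,788 supports reading them this way, given the standard Pocock level. It does not show that every efficacy interim is lost, nor that low incidence alone ends the trial.

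**What to change.** Make the number and its unit agree. Either state the threshold as 380 laboratory-confirmed COVID-19 infections, or state a primary-event count that follows from the assumptions: about 57 at the half-way look under the design effect, saying whether participants who drop out are counted.

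Then reword the clause so that a count below the threshold has a single consequence, either postponing the look or counting towards futility, and check that it fits the sample size re-adjustment described under Strengths and limitations. Which consequence to adopt is the trial team's design choice; the documents do not settle it. Simply deleting the event count would leave the same operative futility rule as now.

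The cost is a wording change. The sample size is unaffected and no participants are added.

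### The sample size pays for one efficacy interim, but the wording of the stopping rule does not exclude running that interim twice

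*Protocol article*

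**What the plan says.** All the relevant text except the allocation ratio is in the protocol article, section Sample size calculation, interim, and final analyses.

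- **What is paid for.** The calculation begins "Considering one interim analysis on efficacy (with the Pocock correction" and gives 3788 per arm, rounded up to 3800. One interim plus the final test is two efficacy tests.
- **When the interim takes place.** The third planned interim, for efficacy and re-estimation, is set at 50% of the target sample size.
- **Benefit rule (2).** The trial stops at the efficacy interim if power is at least 90% and p is below 0.05.
- **Futility rule (3).** The trial stops at the same interim if power is below 10%, p is above 0.05 and the event number falls short of an assumed figure, given in parentheses as 380 primary-outcome events. The parenthesis adds that otherwise "the interim analysis is postponed and repeated when the event number reaches 380 events".

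The section does not say whether rule (2) applies at the repeat, and it gives no alpha adjustment for a repeat.

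**The concern.** Postponing an interim because too few events have accrued is harmless: the arms are compared once, only later. Repeating an interim is different, because something repeated has already been done. Rule (3) uses p and power, which are comparisons between arms, so on its wording those results are in hand at the 50% look before the need for a repeat is settled. If rule (2) is open at both looks, efficacy can be tested at 50%, again at the event trigger, and at the end. That is three chances to declare benefit under a correction for two.

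What is at stake is the 5% two-sided error on which the sample size is based. A stopping rule should fix the number of efficacy comparisons, and this one leaves it open. This is not a detail left to an analysis plan: the protocol states the rule, and the rule does not fit the protocol's own sample-size basis.

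**Working it through.** **1. Reproduce the plan's figure.** The inputs are: "The primary outcome is estimated to occur in 20% of COVID-19-infected cases"; "we hypothesised that our intervention would result in a 50% risk reduction", hence 20% against 10%; "90% power, 5% alpha (superiority design, two-sided"; "a dropout rate of 20" per cent; "assuming 10% incidence of COVID-19 in the target population"; and, from Randomisation and blinding, "The allocation ratio will be 1:1".

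Infected per arm: n = [z_α √(2 × 0.15 × 0.85) + z_β √(0.20 × 0.80 + 0.10 × 0.90)]² / 0.10²

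- At the two-look Pocock level 0.0294 (z = 2.178): (2.178 × 0.505 + 1.2816 × 0.5)² / 0.01 = 303. Then 303 / 0.10 / 0.80 = 3787.5, the printed 3788.
- At 0.05: 266 infected per arm, and 266 / 0.10 / 0.80 = 3325, which does not match.

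The size therefore pays for exactly one efficacy interim.

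**2. Place the repeat on the information scale.** The design needs 2 × 303 = 606 infections. The figure 380 equals 10% of 3800, the infections expected among the 3800 people enrolled at the halfway point. If 380 means infections (an assumption), the repeat falls at 380 / 606 = 0.627 of information. After 20% dropout the halfway look would have 3800 × 0.10 × 0.80 = 304 infections, about 50% of information and short of 380. On that reading the repeat would be triggered on plan.

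**3. Overall two-sided type I error.** This is 1 − P(|Z₁| < c₁, |Z₂| < c₂, |Z₃| < c₃), with the Z's jointly normal and correlation √(tᵢ/tⱼ), for t = 0.50, 0.627 and 1. The same calculation returns Pocock's 0.0294 for two looks and 0.0221 for three equally spaced looks.

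| Criterion | One interim + final | With the repeat |
|---|---|---|
| 0.0294 at every test | 0.050 | 0.059 |
| p < 0.05 at every test | 0.083 | 0.097 |
| p < 0.05 at interims, 0.0294 at the end | 0.067 | 0.083 |
| Observed power ≥ 90% at interims, 0.0294 at the end | 0.030 | 0.030 |
| Observed power ≥ 90% at interims, 0.05 at the end | 0.0503 | 0.0504 |

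Observed power of at least 90% at alpha 0.05 means an absolute z above 1.96 + 1.28 = 3.24. With the first look kept at 50% and 0.0294 at each test, a repeat at 75% gives 0.059 and one at 90% gives 0.057, so the result depends little on when the repeat falls.

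**4. Read 380 literally.** Expected primary-outcome events in the whole trial are 7600 × 0.10 × 0.15 = 114, or 114 × 0.80 = 91 after dropout. With no effect (20% in both arms) they are 7600 × 0.10 × 0.20 = 152 before dropout. None of these reaches 380. That would take an incidence of 380 / (7600 × 0.15) = 33%, or 380 / (6080 × 0.15) = 42% after dropout, or a much larger sample.

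**5. Price of a third look.** At 0.0221 the formula gives 323 infected per arm, and 323 / 0.10 / 0.80 = 4037.5, so 4038 per arm (250 more). With 303 kept, single-test power at 0.0221 is 87.9%.

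**The case against.** The strongest case is that no extra test is intended. The sentence says the analysis is postponed, an event count can be checked without comparing arms, and the repeat sits inside a rule labelled as stopping for futility. A repeat that cannot stop for benefit does not raise type I error. Taken literally, 380 primary-outcome events will not accrue on the plan's assumptions, so the repeat would not arise. And rule (2) is a joint condition: if its power requirement means observed power, the extra look adds almost nothing.

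Much of this stands, and it limits the point. It rules out saying that the plan contains a third efficacy test. It does not settle the matter, for three reasons.

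- The sentence also says the analysis is repeated, and rule (3) reads p and power at the interim.
- The power condition is not defined, so error control cannot rest on it.
- The 380 figure looks like an infection count. Even as an event count it could be reached if incidence were far higher or the sample were enlarged; the Strengths and limitations section allows that incidence may depart from 10%, and re-estimation is planned at this same interim.

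**Conclusion.** The point holds as an unresolved ambiguity with a modest possible cost. The trial is sized for two efficacy tests, and the stopping rule as worded does not exclude three. If the repeat is a second comparison between arms, the p-value decides, and 380 means infections, overall type I error is about 0.059 against 0.050 at the Pocock level, or about 0.097 against 0.083 at the printed p < 0.05.

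A reader might infer two stronger conclusions, and the documents support neither. The first is that the design necessarily adds an uncorrected third test and so exceeds 5%. That fails if the interim is only deferred, if the repeat cannot stop for benefit, if observed power governs, or if 380 is read literally on the plan's assumptions. The second is that the inflation is larger because the first look could come at a small fraction of information. The plan sets that look at 50% of the target sample size and gives no basis for an earlier fraction.

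The rise to 0.083 from testing at p < 0.05 instead of 0.0294 needs no repeat. It is a separate and larger matter.

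**What to change.** State how many efficacy comparisons will be made. Either route works:

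- **(a) One deferred interim.** Check the event count pooled and blinded, make no comparison between arms until the threshold is met, and hold the single efficacy interim then. Deleting the reference to repetition is not enough. Rule (3) now requires the threshold to be unmet, so with a deferred interim it could never be satisfied; its futility condition must be reworded. The threshold must also be reconciled with the expected events, or the interim would not take place on plan. The cost is a delay to the look now planned at 50%; the sample size is unchanged.
- **(b) Two interims.** Keep the 50% look and the repeat, and control alpha over all looks with a Lan-DeMets Pocock-type spending function at the actual information. The cost is slightly stricter levels at later looks and power at the present size slightly below 90% (about 88% at a three-look level of 0.0221), or about 4038 per arm to restore it at that level. Alternatively, state that the repeat is for futility or re-estimation only, with no stopping for benefit.

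Under either route, define the power condition in rules (2) and (3), since the size of the problem depends on it.

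### The plan expects complete primary data from the Ministry under intention-to-treat, yet classes missed calls as dropout unless the participant is hospitalised and sizes the trial as if dropouts supply no primary data.

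*Protocol article*

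**What the plan says.** All of the following stands in the Protocol article, section on sample size calculation, interim, and final analyses, unless noted.

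- **Dropout rule.** Missing more than one consecutive intervention after the initial assessment, or withdrawing consent, "results in the dropout of the patients unless hospitalisation is required in the meantime". The exception names hospitalisation in general; it sets no condition on cause or length of stay.
- **Analysis principle.** In the final analysis, "the intention-to-treat analysis will be favoured over per-protocol (or “as-treated”) analysis".
- **Primary data.** "We expect a full dataset for the primary endpoint (since the Hungarian Ministry of Interior will provide these data"). Should any be missing, the fallback is available case analysis.
- **Sample size.** The calculation allows for "a dropout rate of 20" per cent. The first interim analysis re-estimates the sample size because of the dropout rate, and the Strengths and limitations section presents the adaptive design as a possible answer to unpredictable dropout.
- **Other outcomes.** A last-observation-carried-forward "strategy will be followed to impute missing data for other outcomes measured during the study". Under Strengths and limitations, "All data on secondary outcomes are provided by participants and other, less reliable indirect data sources".
- **Endpoints (Outcomes section).** The primary composite covers ICU admission, hospital admission over 48 h for listed reasons, and death, all in laboratory-verified COVID-19 cases. Numbers of emergency, hospital and intensive care admissions are secondary endpoints.

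**The concern.** Two participants with the same record of missed calls are classed differently according to whether they were hospitalised after randomisation. Hospitalisation overlaps the primary composite and the secondary admission counts, so study status is partly determined by outcome.

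Whether this matters for the primary endpoint depends on what dropout means there, and the section points both ways. Complete Ministry data under intention-to-treat imply that a person who stops answering calls is still counted. A 20% inflation, and a re-estimation driven by dropout, imply that this person is not. The text does not say which applies.

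At stake is who enters the primary comparison. If dropouts are excluded, hospitalised non-callers stay in while well non-callers leave, and a difference in call dropout between arms could then appear as a treatment effect.

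**Working it through.** **1. Reproducing the plan's figure.** Inputs from the sample size section: event risk 20% v 10% in infected participants, 90% power, two-sided 5% alpha, one efficacy interim with Pocock correction (nominal 0.0294 for two looks), 10% incidence, 20% dropout.

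Infected participants per arm, pooled variance, no continuity correction:

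n = [2.178 × √(2 × 0.15 × 0.85) + 1.282 × √(0.2 × 0.8 + 0.1 × 0.9)]² / 0.10² = 302.99, so 303.

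Randomised per arm: 303 / 0.10 / (1 − 0.20) = 3787.5, so 3788. This is the stated figure. Without the dropout term it would be 303 / 0.10 = 3030. The plan therefore budgets for 20% of randomised participants giving no primary data.

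**2. If everyone randomised is analysed from Ministry data.** Call attendance removes nobody. A null relative risk (RR, B over A) stays at 1.00 and the rule adds no bias. On the plan's own assumptions the allowance is then surplus: 3800 per arm gives 380 infected and about 95.5% power at 0.0294, against 90.1% with 304 (380 × 0.80).

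**3. If dropouts are excluded: upper bound.** The documents give no dropout rate by arm, so the arm rates below are assumptions centred on the plan's 20%. Assume also that missed calls are otherwise unrelated to outcome and that every event case is kept. With true risk p and dropout d:

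observed risk = p / [p + (1 − p)(1 − d)]

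For p = 0.20 and d = 0.15: 0.20 / (0.20 + 0.80 × 0.85) = 0.2273. For d = 0.25: 0.20 / (0.20 + 0.80 × 0.75) = 0.2500. The ratio is 1.10.

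With no true effect (20% in both arms), 380 infected per arm before exclusion, and a two-sided 5% test by normal approximation:

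| Dropout A / B | Observed risk A | Observed risk B | RR | Type I error |
|---|---|---|---|---|
| 20% / 20% | 23.8% | 23.8% | 1.00 | 5.0% |
| 15% / 25% | 22.7% | 25.0% | 1.10 | 10.4% |
| 25% / 15% | 25.0% | 22.7% | 0.91 | 10.4% |
| 10% / 30% | 21.7% | 26.3% | 1.21 | 27.3% |
| 30% / 10% | 26.3% | 21.7% | 0.83 | 27.3% |

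At the Pocock level of 0.0294, the 10-point gap gives 6.9%. With all randomised as denominator (risk 0.20 × 0.10 = 2%), 15% / 25% gives RR 1.13 and 25% / 15% gives 0.885, with type I error about 12% at the 5% level. A true RR of 0.50 in infected participants reads as 0.57 (15% / 25%), 0.46 (25% / 15%) or 0.51 (20% / 20%).

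**4. If only some events are kept.** Let r be the share of event cases among would-be dropouts whom the exception retains:

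observed risk = p(1 − (1 − r)d) / [p(1 − (1 − r)d) + (1 − p)(1 − d)]

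Step 3 is r = 1. At r = 0 the null RR is 1.00. At an assumed r = 0.10, 15% / 25% gives 0.155 / 0.755 = 0.2053 over 0.173 / 0.853 = 0.2028, RR 1.01. For 10% / 30% it is 0.146 / 0.706 = 0.2068 over 0.182 / 0.902 = 0.2018, RR 1.02.

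**The case against.** The strongest reply is that the article never says well non-callers leave the denominator. It prefers intention-to-treat, takes the primary endpoint from an outside source, and uses available cases only if those data are missing, which unanswered calls do not cause. Dropout could simply mean leaving the calls, and the exception has an ordinary purpose: a person in hospital cannot take calls and should not be called non-adherent. All of this stands, so a reader who infers that the primary comparison is certainly biased goes beyond the text. What it does not explain is the 20% removed from the analysable number and the re-estimation tied to dropout. Neither is needed if dropouts still supply primary data.

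A reader might also infer that group B will drop out more because its calls last 20 minutes against 10. In the Interventions section those durations describe the first session. The length of follow-up calls is not given, and the dropout rule applies only after the initial assessment. Unequal dropout is possible, but the documents support neither its size nor its direction. Higher dropout in B would in any case push RR upward and hide benefit.

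Nor should the RRs of 1.10 or 1.21 be read as expected values. The exception covers hospitalisation within the missed-call period. Someone who stopped answering months before admission would already be a dropout, and a death outside hospital is not covered. Any hospitalisation is also broader than the endpoint component. Finally, the rise from 20% to 23.8% with equal dropout is not an arm bias, since the null RR stays at 1.00.

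**Conclusion.** The point holds as an internal contradiction together with a badly framed rule. The section expects full primary data for an intention-to-treat analysis, defines dropout partly by an event overlapping the outcome, and sizes the trial as if dropouts were lost.

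The effect on the primary result is conditional. It is nil if all randomised participants are analysed from Ministry data. If dropouts are excluded, a 10-point gap between arms gives at most a null RR of 1.10 or 0.91, with type I error about 10% at the nominal 5% level. That rests on assumed arm rates and on every event case being kept. With one in ten such events kept, the RR is about 1.01.

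Secondary admission outcomes are more exposed, because the Ministry safeguard is not stated for them: reporting may continue for hospitalised non-callers while others are carried forward. A per-protocol set that kept hospitalised non-callers and removed well ones would be exposed in the same way as the primary endpoint in the excluded case.

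**What to change.** Four changes of wording in the sample size and analysis section:

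1. State that missing more than one consecutive call is discontinuation of the intervention, not study dropout.
2. Define study dropout without reference to hospitalisation.
3. State that all randomised participants are analysed for the primary endpoint in their assigned arm from Ministry data, as far as consent allows.
4. Reconcile the 20% allowance with the expected full dataset, either by saying which participants it covers or by restating it. The documents do not show that it covers only withdrawal of consent to data linkage, so that should not simply be asserted.

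Deleting the hospitalisation exception alone is not enough: if dropouts were still excluded, it would discard events among hospitalised non-callers.

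The cost is wording only. The Ministry data source is already planned, and no extra staff or participants are needed. Keeping 3800 per arm would leave a margin in power and would not introduce bias.
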